## Abstract

**Background:**

One of the unfortunate events after bariatric surgery is the weight regain, which occurs in some patients. Food addiction is an eating disorder related to the brain-intestinal axis and can be effective in weight regain after bariatric surgery. In addition, the gut microbiome plays a vital role in eating behaviors, including food addiction. So, this study will aim to evaluate the effects of probiotic supplementation with a weight-reducing diet and cognitive behavioral therapy on anthropometric measures, body composition, eating behavior, and related hormone levels, leptin, oxytocin, and serotonin, in patients with food addiction and weight regain after bariatric surgery.

**Methods:**

We will carry out a triple-blinded randomized clinical trial for 12 weeks to evaluate the effect of probiotic supplementation with a weight-reducing diet and cognitive behavioral therapy on anthropometric measures, body composition, eating behavior, and related hormone levels including leptin, oxytocin, and serotonin, in patients with food addiction and weight regain after bariatric surgery.

**Discussion:**

Based on the available evidence, probiotic supplementation by modifying the intestinal microbiome can improve food addiction and subsequent weight loss.

**Trial Registration:**

Iranian Registry of Clinical Trials IRCT20220406054437N1 Registered on 2022–06-01.

**Supplementary Information:**

The online version contains supplementary material available at 10.1186/s40795-023-00717-w.

## Background

The growing prevalence of obesity in the world has made it a worrying epidemic [1]. Diet therapy, behavioral therapy, drug medication, and surgery treat obesity [2]. Currently, the most important, effective, safe, and long lasting treatment for severe obesity is bariatric surgery [3, 4]. However, not all patients undergoing bariatric surgery can maintain their weight loss, and some experience weight regains [5]. The prevalence of weight regain after bariatric surgery varies depending on the type of surgery, the length of time after surgery, and the definition of weight regain [5, 6]. Different factors affect weight maintenance or weight regain after bariatric surgery, including the type of surgery, eating behavioral disorders, body mass index, eating habits, anatomical changes of the gastrointestinal tract, hormonal changes, gut microbiome changes, access to healthy food, having exercise, and the existence of support groups [7–9]. With weight regain, diseases associated with obesity also return. It is also psychologically unbearable for the patient because the patient feels that he has lost his last way of treatment [6]. Eating disorders are the important factors affecting weight consequences after bariatric surgery, which need to be given more attention [10, 11]. One eating disorder that has recently come to the attention of researchers is food addiction. Food addiction is persistent, uncontrolled overeating of high-calorie foods (high in fat and sugar) associated with activating the brain s dopaminergic system or brain reward system [12]. Food addiction is also associated with other eating disorders such as binge eating and other mental disorders such as depression and anxiety [13–15]. The intestinal microbiome is one of the known influential regions that play an important role in the etiology of many diseases, including obesity; brain-intestinal axis signaling plays an important role in controlling food intake and energy homeostasis, followed by obesity [16]. Normal eating behaviors are coordinated by intestinal balance and extraintestinal hedonic and hemostatic mechanisms [17]. Growing studies on the role of intestinal microbiota in the etiology and progression of eating disorders have been done [18]. Intestinal bacteria can affect appetite control systems by producing metabolites such as lipopolysaccharide and flagellin in several ways: a) Effect on the secretion of digestive hormones such as cholecystokinin b) Effect on the central nervous system c) Increasing the permeability of the blood–brain barrier and increasing the effect of circulating cytokines on the appetite regulation center; Furthermore, intestinal bacteria affect the melanocortin system by producing peptides that mimic the function of neuropeptides such as α-MSH (α-melanocyte-stimulating hormone); bacteria also affect the appetite regulation system by producing neurotransmitters such as serotonin [18, 19]. There is also a correlation between mood, eating behavior, and intestinal microbiota, in that stress and depression increase the consumption of delicious foods; subsequently, it affects the growth of intestinal microbiota [20]. Also, autonomic changes, hormonal changes, and inflammation from stress and depression alter the gut microbiota [20]. Changes in the Brain-Gut-Microbiome system in food addiction shift the balance of the hedonic-homeostatic system toward a hedonic mechanism [17]. Hormones such as leptin, serotonin, and oxytocin, have an important role in the hedonic and homeostatic system and result from eating behaviors and food addiction [21–25]. Increased leptin concentrations are associated with addictive behaviors [26]. Also, intestinal microbiota, influenced by food intake, are effective in leptin expression and resistance [27–30]. Oxytocin is another hormone involved in food intake and eating behaviors [31]. Food intake activates oxytocin neurons in the hypothalamus, and fasting reduces oxytocin levels [32]. Oxytocin receptors are also present in many brain areas, including ventral tegmental and accumbens nuclei. They are involved in the brain reward system and hedonic pathway controlling appetite and food intake [32]. Oxytocin levels are closely related to intestinal microbiota (depletion of intestinal microorganisms leads to a significant reduction in oxytocin levels; also, Lactobacillus reuteri is involved in modulating oxytocin) [33–35]. Serotonin is another hormone that is effective in both the homeostatic and hedonic systems of food control [36]. Serotonin receptors are expressed in the dorsal striatum, an important area in eating behavior [36]. Activating the serotonin receptor reduces dopaminergic signaling and the desire for food intake [36]. The gastrointestinal tract contains a significant portion of serotonin, and the gut microbiota plays an important role in regulating serotonin; spore-forming bacteria lead to the synthesis of serotonin in enterochromaffin cells [37]. Serotonin is also involved in the development of food addiction; Low levels of serotonin in the brain lead to overeating delicious and sugar-rich foods, and increased blood glucose levels lead to increased absorption of the amino acid tryptophan and ultimately increase serotonin levels [38]. Bariatric surgery leads to anatomical, neurological, and physiological changes affecting the signaling of the homeostatic and hedonic systems, as well as changes in gastrointestinal hormones and intestinal microbiome, which profoundly affect eating behavior and subsequent weighting consequences [39]. Few interventions have been performed to deal with weight regain, mainly in medication, reoperation, and behavioral therapy. Researchers are also looking for ways to deal with regaining weight after bariatric surgery. Various studies have been performed on the effectiveness of probiotics on anthropometric indices, hormone levels, and eating behavior In obese people without surgery [40–43]. To date, no study has been performed on the effect of probiotics on people with food addiction and weight regain after bariatric surgery. The prevalence of food addiction in people who have undergone bariatric surgery is reported to be between 14–58% [44, 45]. Due to the significant prevalence of food addiction in patients undergoing bariatric surgery and its effect on the weight consequences of these patients, as well as changes in the intestinal microbiome and the role of the intestinal microbiome in hormonal changes and its relationship with food addiction, and, there are several studies on the effectiveness of probiotics in intestinal microbiota balance and improving food addiction and weight management in obese patients without bariatric surgery, therefore In this clinical trial study, the effect of probiotic supplementation on the improvement of outcome measures of weight control and levels of leptin, oxytocin, serotonin, followed by the improvement of food addiction and weight management of patients with food addiction and weight regain after bariatric surgery has been surveyed.

### Objectives and hypothesis

This study aims to investigate the effect of probiotic supplementation with a weight-reducing diet and psychotherapy intervention on anthropometric measures, body composition, eating behavior, and related hormone levels (leptin, serotonin, oxytocin) in patients with food addiction and weight regain after bariatric surgery.

## Methods and design

### Study design

We will conduct a 12-week triple-blind randomized clinical trial. The flow chart of the study is presented in Figs. 1 and 2. This intervention will be performed in the nutrition clinic of Shahid Beheshti University of Medical Sciences in Tehran, Iran, to evaluate the effect of probiotic supplementation with a weight-reducing diet and psychotherapy on anthropometric measures, body composition, eating behavior, and related hormone levels in patients with food addiction and weight regain after bariatric surgery. The protocol is written in line with the Standard Protocol Items Recommendations for Interventional Trials (SPIRIT) checklist (Additional file 1) [46].

**Fig. 1 Fig1:**
[figure not shown]
Protocol flow diagram; we will carry out a 12-week randomized controlled trial to determine the effects of probiotic supplementation with weight reducing diet on anthropometric measures, body composition, eating behavior, and related hormone levels in patients with food addiction and weight regain after bariatric surgery

**Fig. 2 Fig2:**
[figure not shown]
Timeline of the study; we expect the duration of the trial will be 20 months

### Sample size

The number of samples required for this study was calculated based on weight as a main dependent variable. The results of a previous study were used to calculate the sample size [47]. Sample size was calculated with α = 0.05 and power of 80% (1-β = 0.8). the sample size in each group was determined to be 20 patients; assuming a drop of 20%, 25 patients will be admitted to each group.

$$\begin{array}{c}\mathrm S1=2.8\\\mathrm S2\;=2.9\\\mathrm{Sp}\;=\;8.125\\\mathrm\mu1-\mathrm\mu2=2.5\\\end{array}$$

$$\begin{array}{c}\mathrm n=\frac{2\mathrm{Sp}^2\left({\mathrm Z}_{1-{\displaystyle\frac{\mathrm a}2}}+{\mathrm Z}_{1-\mathrm\beta}\;\right)^2}{\left(\mathrm\mu1-\mathrm\mu2\right)^2}\end{array}$$

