### Randomization

This study is a triple-blind randomized controlled clinical trial. A simple method has been used for randomization. The randomization unit is Individual. Excel software has been used for randomization. Using unique codes as ID numbers, using random numbers generated by the software, participants were randomly assigned to the same volume in the intervention and placebo groups. (Description of randomization by Excel software: In the first step, we generated 50 random numbers according to the sample size, in the next step, we obtained the rank of these numbers obtained in the first step, and in the third step, we divided these numbers by 25, in the fourth step, the numbers that fell between zero and one were in the intervention group and the rest in the placebo group) The primary service method was used for allocation concealment, and someone outside our study performed allocation concealment and labeling of supplements.

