### Statistical analysis

In this study, data analysis will be performed by using SPSS version 21.0 (SPSS Inc, Chicago, Illinois) software. A paired t-test will be used to compare the mean of quantitative variables with normal distribution in each group between the beginning and the end of the study. The t-test will be used to compare the mean between the two groups at the beginning and end of the study. In the case of quantitative variables with non-normal distribution, Wilcoxon and Mann–Whitney tests are used, respectively. A repeated ANOVA test will be used for the variables measured three times during the study. Covariance analysis will be used to eliminate the effect of quantitative confounding factors. Quantitative confounding factors are physical activity and baseline values of the biochemical markers. A Chi-square test will be used to compare the qualitative variables between the two groups, and regression analysis will be used to eliminate the effect of qualitative confounding.

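### The sample-size section prints the pooled variance 8.125 as Sp; separately, 20.41 was rounded down to 20, so power is 79% by the plan's formula and about 77% by the t-test, not 80%

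*Protocol article*

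**What the plan says.** The Sample size section of the protocol article states that the number was "calculated based on weight as a main dependent variable", with inputs taken from an earlier study. The error rates are given as "Sample size was calculated with α = 0.05 and power of 80" per cent. The displayed inputs are S1 = 2.8, S2 = 2.9, Sp = 8.125 and μ1 − μ2 = 2.5. The displayed formula is n = 2·Sp²·(Z(1−α/2) + Z(1−β))² / (μ1 − μ2)², so the test is two-sided and Sp enters squared. The result is that "the sample size in each group was determined to be 20 patients", and then, "assuming a drop of 20%, 25 patients will be admitted to each group".

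The Randomization section gives equal arms: "participants were randomly assigned to the same volume in the intervention and placebo groups". The Statistical analysis section names the between-group test for normally distributed quantitative variables: "The t-test will be used to compare the mean between the two groups at the beginning and end of the study".

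**The concern.** A pooled standard deviation must lie between the two standard deviations that it pools. A value of 8.125 next to 2.8 and 2.9 therefore cannot be an SD, and the section contradicts itself on the input that drives the sample size. A reader who puts the printed Sp into the printed formula gets a number about eight times the one stated, and cannot tell from that line whether the trial is properly sized or far too small.

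Apart from the label, the stated 20 is also slightly below what the formula returns, so the claimed 80% power is not reached at the number of evaluable patients the plan itself expects. What is at stake is whether the published calculation can be followed and whether its power statement is accurate. Whether the trial is viable is not in question.

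**Working it through.** **Inputs** (all from the Sample size section unless noted): two-sided α = 0.05, so Z = 1.960; power 80%, so Z = 0.842; S1 = 2.8; S2 = 2.9; difference 2.5; 1:1 allocation (Randomization section); two-sample t-test (Statistical analysis section).

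**1. What 8.125 is.** With equal arms the pooled variance is (S1² + S2²)/2 = (7.84 + 8.41)/2 = 16.25/2 = 8.125, exactly the printed figure. So Sp² = 8.125 and Sp = √8.125 = 2.85.

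**2. The plan's own figure.** (1.960 + 0.842)² = 7.849. Taking Sp² = 8.125:

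n = 2 × 8.125 × 7.849 / 2.5² = 20.41 per arm.

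With the coarser values 1.96 and 0.84 it is 20.38. Either way the stated 20 is this result rounded down; the smallest whole number that meets the target is 21.

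**3. The line taken literally.** With Sp = 8.125, squared as the formula requires:

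n = 2 × 8.125² × 7.849 / 6.25 = 165.8, so 166 per arm.

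This is nowhere near 20, so the calculation was evidently done with Sp² = 8.125 and only the label is wrong.

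**4. Power at 20 evaluable per arm, by the plan's normal formula.** Standard error of the difference = 2.85 × √(2/20) = 0.901. Then 2.5/0.901 = 2.774, and power = Φ(2.774 − 1.960) = 79.2%.

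**5. Power by the two-sample t-test** (noncentral t, 2n − 2 degrees of freedom, SD 2.85, difference 2.5):

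| Evaluable per arm | Power, normal formula | Power, t-test |
|---|---|---|
| 20 | 79.2% | 77.1% |
| 21 | 81.1% | 79.2% |
| 22 | 82.9% | 81.1% |
| 25 | 87.3% | 86.0% |

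So 21 per arm are needed by the formula and 22 by the t-test.

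**6. Where the shortfall comes from.** Rounding down accounts for 80.0 − 79.2 = 0.8 points. Using a normal approximation for a t-test accounts for 79.2 − 77.1 = 2.1 points. The mislabelled Sp accounts for none of it.

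**7. Difference detectable with 80% power at 20 per arm.** By the normal formula, 2.802 × 0.901 = 2.53; by the t-test, 2.59. The plan uses 2.5.

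**8. Dropout step.** 20/(1 − 0.20) = 25, which is the right form of the inflation and matches the text.

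**The case against.** The strongest reply is that the calculation is essentially sound. S1, S2, the difference, α, the power and the printed formula together give 20.41, so the stated number can be recovered without the faulty line. One patient per arm is a small rounding matter, and a normal-approximation formula is a conventional choice for sizing a trial, not a mistake in arithmetic. This stands, and it limits the point to a correction of wording and of the power figure.

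Two further caveats also stand. The t-test is not clearly the decisive analysis for weight: weight is measured at three visits, and the Statistical analysis section also provides for repeated-measures ANOVA and analysis of covariance. The 77% is therefore conditional on the t-test. The Sample size section also does not say whether 2.8 and 2.9 are SDs of change or of end values, and it gives no unit.

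A lost superscript in the input line is conceivable, since exponents are lost elsewhere in the text available here (the CFU counts). It is not demonstrated, because the exponent on Sp survives in the formula just below. If that is the explanation, the relabelling falls away and the rounding remains.

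Two stronger readings are tempting and fail. One is that the trial needs 166 per arm, or that the misprint caused the fall in power. The figure of 166 requires an SD of 8.125 and the 77% requires an SD of 2.85, so they cannot both hold; with an SD of 8.125, power at 20 per arm would be about 16%. S1 and S2 show that 2.85 is the SD meant. The other is that the 25 enrolled per arm rescue the claim, with 86% power. The Adherence section restricts analysis to patients with more than 90% adherence and the plan itself expects 20 per arm to remain, so 86% does not describe the stated analysis.

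**Conclusion.** The point holds as two separate, minor errors. The printed Sp is the pooled variance; this makes the input line inconsistent with its neighbours and with the formula, but it did not enter the result. Independently, 20.41 was rounded down, so at 20 evaluable per arm the power for a difference of 2.5 is 0.8 points below the stated 80% by the plan's own formula and 2.9 points below it by the t-test. These figures assume equal arms, two-sided α = 0.05, exactly 20 analysed per arm, and that the SD of 2.85 applies to the quantity actually tested. The label error and the rounding are certain from the printed inputs; the 77% depends on the t-test being the analysis of weight.

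**What to change.** In the Sample size section, replace the input line with: Sp² = 8.125 (Sp = 2.85). Then restate the power, for example: with 20 evaluable patients per arm, power for a difference of 2.5 is about 77% by two-sample t-test (79% by the normal-approximation formula). Equivalently, state that 20 per arm give 80% power for a difference of about 2.6. Say in the same place which quantity the SD of 2.85 refers to (change or end value) and in what unit, since the restated power depends on it.

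Enrolment of 25 per arm does not need to change. The 86% for 25 per arm should be quoted only if the plan is amended to analyse all randomised participants.

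The cost is a few corrected words and a slightly less favourable power figure.

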### Study population

Patients with weight regain after bariatric surgery, and food addiction will be recruited from the Obesity Surgery Center of Sina Hospital and Rasoul Akram Hospital in Tehran.

Weight regain in this study was defined as: At least 18 months have passed since the surgery, and at least 10% of the lowest weight has returned. The diagnosis of food addiction will be based on the Food Addiction Questionnaire (Modified Yale Food Addiction Scale; mYFAS 2.0) [48]. Subjects who meet the inclusion criteria will be thoroughly informed about the protocol of the study. In addition, each participant will sign the informed consent form.

### Inclusion and exclusion criteria

For this study, 50 patients with weight regain and food addiction and with the following inclusion criteria will be included in the study: aged 18–50 years; BMI ≥ 25 kg/m2; willingness to participate in the study; not having diseases such as cancer, thyroid, renal or liver (except fatty liver); non-pregnant or lactating or menopause or professional athlete; not use of any antibiotics in the last three weeks and any protein or probiotic supplement in the last month.

Patients will be excluded if: taking any antibiotics during the study; using probiotic products (probiotic supplements, yogurt, cheese, cakes, biscuits, and probiotic pasta) or protein supplements during the study; using weight-loss or appetite-suppressing medications; pregnancy; consuming less than 90% of the supplements prescribed during the study Also, we will exclude participants who refuse to continue the study.

### Randomization

This study is a triple-blind randomized controlled clinical trial. A simple method has been used for randomization. The randomization unit is Individual. Excel software has been used for randomization. Using unique codes as ID numbers, using random numbers generated by the software, participants were randomly assigned to the same volume in the intervention and placebo groups. (Description of randomization by Excel software: In the first step, we generated 50 random numbers according to the sample size, in the next step, we obtained the rank of these numbers obtained in the first step, and in the third step, we divided these numbers by 25, in the fourth step, the numbers that fell between zero and one were in the intervention group and the rest in the placebo group) The primary service method was used for allocation concealment, and someone outside our study performed allocation concealment and labeling of supplements.

### Implementation

Potential participants will be invited to the study by [name] and AZ. The sequencing will be generated by AS, who is not going to assign participants into the study.

### Intervention

For all participants in this study, the standard hypocaloric diet (-300 to -500 kcal from total energy requirement) is calculated based on basal metabolism (use of indirect calorimeter) and level of physical activity. The diet in each group will consist of 45% carbohydrates, 25% protein, and 30% fat. For all participants in the study, ten one-hour online individual sessions, once a week, will be performed cognitive behavioral therapy (CBT) intervention by a psychologist. This study will randomly divide participants into groups receiving a probiotic supplement or placebo. All participants are asked to take 2 capsules daily (after breakfast and after lunch) for 12 weeks. Capsules are given to participants at the beginning of the study and in the sixth week of the study, and they are asked to return the unused capsules. To follow the participants and ensure their adherence to diet and receive supplements, participants will be contacted by telephone once a week. Also, the participants will be followed up and evaluated in person at the end of the sixth and twelfth weeks. Because multi-strain probiotics are more effective than single-strain probiotics [49, 50], multi-strain probiotics will be used in this study. Each probiotic capsule contains Lactobacillus acidophilus (1.8 × 109 CFU / capsule), Bifidobacterium bifidum (1.8 × 109 CFU / capsule), Bifidobacterium lactis (1.8 × 109 CFU / capsule), Bifidobacterium longul / C, 1.8 (1 × 109 CFU / capsule), Lactobacillus reuteri (1 × 109 CFU / capsule), magnesium stearate and maltodextrin. The placebo capsule contains 300 mg of starch. The capsules are similar in shape, size, and color and are provided by Takgen Zist Company in Iran.

